### Sample size calculation

The sample size was calculated based on the null and alternative hypotheses, together with the type-I and type-II errors defined as follows:

Null hypothesis (H_0_): the additional dose of IVM is not more effective than the standard single dose per annum treatment (i.e. Treatment – Control = 0).

Alternative hypothesis (H_A_): the additional dose of IVM is more effective than the standard dose (i.e. Treatment − Control > 0).

The type-1 error rate (*α*), i.e. rejecting H_0_ when it is true, is set at 0.05, with a two-sided test. To control for type-II error (*β*), the probability of rejecting H_0_ when it is false is set at 0.80, taking into consideration budget allocation.

The hotspot districts have been receiving an annual single dose of IVM for the past 15 years with the prevalence rates ranging between 1% and 18.2%. Therefore, it is assumed that the new intervention would have an effect, expected to be larger than the effect of the standard control approach, with an effect size of 0.4. Based on these assumptions, the sample size was calculated using the Optimal Design software [34]. Thus, for 0.80 power the study requires a cluster size of 58.

With an expected non-response and a loss to follow-up of 37% (determined from previous unpublished studies), the sample size per cluster has been determined to be 80. With 18 clusters to be surveyed, a total of 1440 study participants, from the two study districts, will be expected to take part in this trial.

Study participants will not be paid as part of the survey. However, in order to mitigate the high dropout rates during follow-ups, participants will be compensated for the time lost for working during the days they are participating in survey activities, with an amount of 7 Cedis (equivalent to US$1.61). They will also be contacted at 14 days and 7 days prior to follow-up, in order to ensure their availability. Even though there is always the possibility of emergencies and other social responsibilities that may result in their unavailability, efforts will be made to reach them.

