### Cluster randomisation

Randomisation will be stratified by the prevalence of LF (as determined in the baseline surveys). The randomisation sequence generation will be undertaken by an independent statistician using computerised random-number generation. Sealed envelopes containing cluster identification will be placed in pre-stratified ballot boxes, with community leaders invited to select envelopes from the boxes and directed to put the selected envelope in a box labelled A or B (corresponding to the two study groups, each with nine clusters) according to the pre-generated randomisation sequence for that stratum. With an average household size of six and the frequency of under 5 years being 14.3%, 45 households will be randomly selected in each cluster and five eligible household members recruited into the cross-sectional surveys. Owing to the nature of the interventions, participants will not be blinded to their group randomisation. However, the identity of the study groups will remain hidden until the completion of community sensitisation and randomisation in order to eliminate participation bias. Further, the laboratory technicians conducting the parasitological examinations and the statistician responsible for analysis will be blinded to the group assignment. The blinding to the laboratory technicians and statistician will be done using sample/study participant identification codes for samples and results which will not be linked to the study groups.

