#### Analysis strategy

Each of our study outcomes, i.e. prevalence and intensity of *W. bancrofti* mf, will be considered separately during the analysis. Loss to follow-up was taken into consideration during our sample size calculation. Therefore, regardless of the number of incomplete observations, we expect to end up with no less than 58 complete observations per community at the end of the study.

A panel of individual line plots for the study participants would be used in the assessment of within-person variability. Since the assumptions of likelihood are violated by the effect of within-group and within-subject clusters in longitudinal data, in assessing the transmission dynamics of LF infection, the measured covariates will be regressed separately on both the prevalence and the intensity of infections using a quasi-likelihood method, i.e. generalised estimating equations, which uses an association matrix instead of the diagonal matrix employed by the generalised linear models. As part of the model validation, the point-referenced residuals of the provisional models will be assessed for spatial autocorrelation. The results of this assessment would help to determine if unmeasured/unobserved factors in the study areas play relevant roles in the transmission dynamics of LF infections. Using classical geostatistical concepts, our final model would be adjusted for both the effects of the measured and unobserved factors.

For entomological endpoints, infection rates will be determined, using the polymerase chain reaction (PCR) [40] and LAMP [41] methods. The results will be analysed using the poolscreening software by Katholi and colleagues [42, 43].

The findings and data from this study will be used to develop a mechanistic model, which describes the variability in treatment responses in populations. This will be implemented into an already available and well-established transmission dynamic model for LF (LYMFASIM) [44, 45], which will then be used to systematically explore the consequence of twice-yearly treatment on the long-term impact of MDA and elimination prospects. LYMFASIM simulates the spread of *W. bancrofti* in a human community and the impact of control measures, with the advantage of accounting for a variety of parameters specific to the population of interest and output predictions [45, 46].

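### The 80 per cluster adds the 37% loss to 58 instead of dividing by the share retained, so the stated floor of 58 completers does not follow from the plan's own figures

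*Protocol article*

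**What the plan says.** All the figures are in the protocol article.

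- **Sample size calculation, required number:** "for 0.80 power the study requires a cluster size of 58". The type I error rate "is set at 0.05, with a two-sided test", and the effect size is 0.4. Neither the scale of the 0.4 nor an ICC is given.
- **Sample size calculation, attrition:** "With an expected non-response and a loss to follow-up of 37% (determined from previous unpublished studies" is the allowance, and from it "the sample size per cluster has been determined to be 80".
- **Sample size calculation, total:** "With 18 clusters to be surveyed, a total of 1440 study participants". Table 2 repeats 1440 as the target sample size.
- **Cluster randomisation:** the 18 clusters are split equally, "corresponding to the two study groups, each with nine clusters". The same section describes field recruitment of 45 households per cluster with five eligible members each.
- **Secondary outcomes, Analysis strategy:** after noting that loss was allowed for in the sample size, it says of the study's close that "regardless of the number of incomplete observations, we expect to end up with no less than 58 complete observations per community".
- **Sensitisation and recruitment:** households are drawn at random until each village's sample size is reached.

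**The concern.** The figures 58, 37% and 80 do not fit together if 37% is a loss rate, which is how the article describes it. Adding 37% to the required number differs from enrolling enough people that 58 remain after 37% are lost, and at this level of loss the two results are well apart (80 and 93).

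Two statements depend on this step. The 0.80 power is tied to 58 analysable people per cluster. The Analysis strategy also repeats 58 as a floor for every community, whatever the number of incomplete observations. Under the plan's own attrition figure, the target of 80 supports neither. The count of people with follow-up matters because the pre-post analysis of the primary outcome uses each participant's change from baseline, to which someone without a follow-up measurement cannot contribute.

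**Working it through.** **Inputs from the article:** required cluster size 58; combined non-response and loss 37%; inflated cluster size 80; 18 clusters, nine per arm; two-sided alpha 0.05; effect size 0.4.

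**1. Reproduce the stated figure.** n × (1 + d) = 58 × 1.37 = 79.46, rounded up to 80, and 80 × 18 = 1440. Both stated numbers are matched.

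**2. Inflation that would keep 58.** n / (1 − d) = 58 / 0.63 = 92.06, rounded up to 93, and 93 × 18 = 1674. Rounding does not bridge 80 and 93.

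**3. What 80 delivers if the full 37% applies to it.** 80 × 0.63 = 50.4 per cluster, and 18 × 50.4 = 907 in total. The plan's 58 implies 18 × 58 = 1044. The shortfall is 1 − 50.4/58 = 13%.

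**4. The loss rate at which 80 leaves 58.** 1 − 58/80 = 27.5%.

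**5. Chance that one cluster still reaches 58.** With 80 enrolled and independent losses at 37%, P(X ≥ 58) for X ~ Binomial(80, 0.63) is about 4.8%.

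**6. Effect on power (conditional).** The article gives no ICC and no scale for the effect size. Two assumptions are made: 0.4 is a standardised mean difference, and the test is a two-arm cluster t test with 18 − 2 = 16 degrees of freedom. With m people per cluster and ICC ρ, the noncentrality is

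0.4 × √18 / (2 × √(ρ + (1 − ρ)/m)).

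Solving for power 0.80 at m = 58 gives ρ ≈ 0.065. At that value the noncentrality is about 2.98 for m = 58 and 2.94 for m = 50. Over a range of assumed ICCs:

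| Assumed ICC | Power at 58 | Power at 50 | Drop (points) |
|---|---|---|---|
| 0.01 | 0.998 | 0.996 | 0.2 |
| 0.02 | 0.985 | 0.979 | 0.6 |
| 0.05 | 0.871 | 0.858 | 1.3 |
| 0.065 | 0.800 | 0.788 | 1.2 |
| 0.10 | 0.650 | 0.641 | 0.9 |
| 0.15 | 0.502 | 0.497 | 0.5 |
| 0.20 | 0.407 | 0.404 | 0.3 |

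The drop is at most about 1.3 points over this range. It is small because the number of clusters limits precision more than the number of people in each.

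**7. The other recruitment figure.** 45 × 5 = 225 per cluster, and 225 × 0.63 = 142. This is far from 80 before loss and from 50 or 58 after it.

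**The case against.** The strongest case is that the full 37% may not fall on the 80.

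- **Replacement in the field.** Households are drawn until the village sample size is reached. If 80 means people actually recruited, initial non-response is replaced and only loss to follow-up reduces the 80. The article does not split the 37%, so this cannot be ruled out, and 50 is the figure when all of it applies after enrolment. The article nevertheless reaches 80 by applying the combined rate to 58, and it never states a lower rate after enrolment.
- **An inflation factor.** The 37% may have been meant as a mark-up. The text calls it expected non-response and loss, so the wording would then be wrong.
- **Retention measures.** The article plans compensation for lost time and contact 14 and 7 days before follow-up. If these brought loss down to 27.5%, 80 would leave 58. So 58 is not impossible; it is just not expected at 37%.
- **Cross-sectional surveys.** The primary outcome is described as measured by cross-sectional surveys. Attrition from the 80 applies in full only if the same people are followed, as the pre-post analysis implies.
- **Larger field recruitment.** With 225 per cluster, about 142 would remain, well above 58. That number conflicts with 80 and 1440, so it does not support the calculation.

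A reader might also infer three stronger things, none of which the documents support. The first is a serious loss of power; the calculation shows about one point. The second is that the Analysis strategy sets incomplete observations aside; it states an expected count and gives no rule for missing data. The third is that the 37% comes from the fall from 48 to 30 people in Table 1, so that loss by 30 months would be larger; the article attributes the 37% only to unpublished studies and does not link it to that table.

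**Conclusion.** The point holds as an arithmetic inconsistency in stated figures. The 80 comes from adding 37% to 58. If the 37% applies in full to those enrolled, about 50 completers per cluster are expected, 13% fewer than 58, and the assurance of at least 58 in every community does not follow. It would hold in expectation only with a loss of 27.5% or less after enrolment, a rate the article does not give.

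The arithmetic on 58, 37% and 80 needs no outside assumption. The figure of 50 assumes that the whole 37% acts on the 80 and that the same people are followed. The power figures assume a standardised effect and an ICC that the article does not state. On those terms the cost is about one point of power. The text is wrong as written and should be corrected, but the design, the test and the allocation are unaffected.

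**What to change.** Choose one of two corrections to Sample size calculation and to the Analysis strategy under Secondary outcomes.

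1. **If 37% is the loss among those enrolled:** state that 80 enrolled gives about 50 completers per cluster (about 907 in total), report the power at 50 with the ICC and effect scale used, and remove the assurance of at least 58.
2. **If the 37% includes non-response replaced during recruitment, or was meant as an inflation factor:** say so, and state the loss rate that applies after enrolment. For 58 to hold it can be at most 27.5%.

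In either case, reconcile 80 per cluster and 1440 in total with the 45 households × 5 members (225 per cluster) under Cluster randomisation, and make clear which number is recruited.

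The cost is a text correction and, under the first option, a slightly less favourable stated power. Extra enrolment is not needed. Only if 58 completers are wanted at a 37% loss would the enrolment figure become 93 per cluster (1674 in total).

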### Treatment interventions

All study groups will receive treatment with 400 μg/kg IVM + 400 mg ALB, which is highly efficacious against *W. bancrofti* [1]. The difference between the study groups is the frequency of treatment provided (Table 3). The MDA will be implemented in all communities as part of the ongoing NTDP. In Ghana, MDA started in the year 2000 as part of the GPELF. Treatment with 400 μg/kg IVM + 400 mg ALB is provided annually by trained CDDs. Every year, the national team organises training for regional, district, subdistrict supervisors, CDDs and their supervisors. They are also taken through their roles and responsibilities. The programme targets all eligible individuals aged 5 years and above in all endemic districts and communities. The strategies follow the door-to-door Directly Observed Treatment (DOT) strategy [35]. This study will follow the exact MDA strategy used by the NTDP and no modifications other than the frequency of treatment will be made. All treatments will be undertaken through the systems established by the NTDP. Further, the onchocerciasis programme in Ghana undertakes twice-yearly treatment with IVM in hyperendemic areas, and the twice-yearly treatment in LF-endemic areas will be an extension of the onchocerciasis program.

**Table 3 Tab3:** Drug dosage and schedule

Arms	Assigned interventions
Control group	400 μg/kg ivermectin + 400 mg albendazole tablets given every year for 2 years
Expanded frequency group	400 μg/kg ivermectin + 400 mg albendazole tablets given every 6 months for 2 years

Routinely, treatment by the NTDP is done from house to house. CDDs also visit schools to treat after prior notification. Treatment is also done at the markets and sometimes at the church and mosque. Work in the districts is monitored and supervised by coordinators. The team supervisors supervise five or six teams, each of which is made up of two CDDs. Communities are demarcated into sections and marked according to days they are to be visited. Teams under a supervisor work in demarked sections in a ‘sweeping’ fashion one after the other each day (i.e. the whole group move to a section, finish the work there and move to the next). The last day is used to ‘mop up’ though all the sections of the area to which the group has been allocated.

### Drug manufacturers and supply

Ivermectin is manufactured by Merck & Co. Ivermectin for the control of elephantiasis and onchocerciasis is donated to national disease elimination programmes for free. At the London Declaration in 2012, the World Health Organisation (WHO) together with pharmaceutical companies and donors committed to: ‘Sustain, expand and extend programmes that ensure the necessary supply of drugs and other interventions to help eradicate Guinea worm disease, and help eliminate by 2020 lymphatic filariasis, leprosy, sleeping sickness (human African trypanosomiasis) and blinding trachoma’. As such, the drugs used by the Ghana Neglected Diseases Programme of the Ghana Health Service, are procured through the systems established by the WHO. As such every year, depending on the target population to be treated, the NTDP formally requests the supply of drugs from the WHO. The WHO facilitates the supply of the IVM and ALB for LF-elimination programmes. A joint mechanism and a set of forms have been developed to facilitate the process of application, review and reporting. The request forms are signed by the NTD programme manager to formally endorse the request for the drugs, and submitted to the WHO country office, with electronic copies to [contact] and the concerned regional focal point, no later than 15 August of the year preceding the year for which medicines are intended to be used (e.g. at the latest by 15 August 2017 for implementation of preventive chemotherapy in 2018) but at least 6 − 8 months before the planned intervention(s) to allow time for reviewing and approval of the request, placing order, drug manufacturing and shipment to the country. All drug request forms are available at http://www.who.int/neglected_diseases/preventive_chemotherapy/reporting/en/.

The request is submitted to the WHO AFRO for review by the Regional Programme Review Group (RPRG), i.e. a technical review committee convened by the AFRO Regional Office as part of the Joint Application Package (JAP). After the RPRG’s approval the request is submitted to the WHO Headquarters (WHO HQ) in Geneva which proceeds to order the shipment after satisfying themselves regarding the approved request. The WHO HQ is responsible for the procurement process. The drug company, after receiving the request, ships the consignment from door to door, i.e. from the factory to the Central Medical Stores (CMS) in Ghana. Countries need to provide tax exemptions for the shipment before the drugs are shipped to the country. In Ghana, the WHO office facilitates the tax exemption process and receives the consignment of drugs on behalf of the programme and then hands over the consignment to the program.

Once the country takes over the drugs in the CMS, a distribution list for regional distribution and a request are sent to the Head of the CMS who proceeds to distribute the drugs to the Regional Medical Stores which then distribute the drugs to the districts, then to the subdistricts and then eventually to the CDDs who do the house-to-house distribution of drugs during the MDAs. Below the regional level, disease-control officers take charge of the drugs and their distribution to the next level.

### Cluster randomisation

Randomisation will be stratified by the prevalence of LF (as determined in the baseline surveys). The randomisation sequence generation will be undertaken by an independent statistician using computerised random-number generation. Sealed envelopes containing cluster identification will be placed in pre-stratified ballot boxes, with community leaders invited to select envelopes from the boxes and directed to put the selected envelope in a box labelled A or B (corresponding to the two study groups, each with nine clusters) according to the pre-generated randomisation sequence for that stratum. With an average household size of six and the frequency of under 5 years being 14.3%, 45 households will be randomly selected in each cluster and five eligible household members recruited into the cross-sectional surveys. Owing to the nature of the interventions, participants will not be blinded to their group randomisation. However, the identity of the study groups will remain hidden until the completion of community sensitisation and randomisation in order to eliminate participation bias. Further, the laboratory technicians conducting the parasitological examinations and the statistician responsible for analysis will be blinded to the group assignment. The blinding to the laboratory technicians and statistician will be done using sample/study participant identification codes for samples and results which will not be linked to the study groups.

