**Fig. 2 Fig2:**
[figure not shown]
Standard Protocol Items for Randomised Trials (SPIRIT) Figure – Schedule of enrolments, interventions and assessments

**Table 2 Tab2:** Trial registration data

Data category	Information
Primary registry and trial identification number	ClinicalTrials.gov, ID: NCT03036059
Date of registration in primary registry	26 January 2017
Secondary identifying numbers	Ghana Health Service Ethics Review Committee: 04112/2016 Noguchi Memorial Institute for Medical Research IRB: CPN 062/16-17
Source(s) of monetary or material support	EDCTP grant TMA 2015 CDF - 976
Primary sponsor	Noguchi Memorial Institute for Medical Research
Contact for public queries	[name]
Contact for scientific queries	[name], [name], [name]
Public title	Twice Yearly Treatment for the Control of LF
Scientific title	Cluster Randomised Community-based Trial of Annual Versus Biannual Single-dose Ivermectin Plus Albendazole Against Wuchereria Bancrofti Infection in Human and Mosquito Populations
Country of recruitment	Ghana
Health condition(s) or problem(s) studied	Lymphatic filariasis
Interventions	400 μg/kg ivermectin + 400 mg albendazole tablets given once or twice a year
Key inclusion and exclusion criteria	Inclusion criteria: residency in endemic community for at least 12 months; willingness to provide informed consent/assent; willingness to donate blood (per the protocol) Exclusion criteria: recent residents (<12 months) in the study districts; inability to give informed consent due to illness, serious medical problems or refusal to participate in the study; pregnancy; children below the age of 5 years
Study type	Interventional allocation: randomised Masking: no masking, open label
Date of first enrolment	19 May 2017
Target sample size	1440
Recruitment status	Recruiting
Primary outcome(s)	Change from baseline prevalence of lymphatic filariasis at 12, 24 and 30 months
Key secondary outcome(s)	Longitudinal assessment of transmission dynamics of lymphatic filariasis. Evaluation of community acceptability of twice-yearly treatment. Feasibility of scale-up of twice-yearly treatment

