### Sensitisation and recruitment

Key stakeholders will be involved in the study and its design. Prior to implementation, meetings will be held with the NTDP, and at each study site, where key stakeholders (chiefs, community leaders and study participants) will be sensitised about the study objectives, interventions, evaluation procedures, and requested to provide input as well as the need for their participation in the study. Community meetings will be held to describe the purpose of the study, the interventions, the evaluation procedures to be followed, and the risks and benefits associated with participation. Individuals will have the opportunity to ask questions for which answers will be provided by the research team.

Consent for the intervention will be provided at the community level with the option for individuals to opt out. Community drug distributors (CDDs) used by the NTDP will number all houses and update their community registers through coordination with the chiefs and village elders. Using a random number generator in Excel, households will be selected until the sample size for each village is attained. Subsequently, households selected for inclusion into the study will be visited by field staff, for consenting and recruitment into the study. In each household visited, written informed consent to conduct the household-level questionnaire will be sought from the household head. Individual-level consent will be sought from selected individuals, 18 years old and above (either for themselves or their children) and written assent sought from children aged 12–17 years.

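### The household sampling rule yields 225 people per cluster (4050 in all), while the sample size section and the registered target set 80 per cluster (1440), and nothing reconciles them

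*Protocol article*

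**What the plan says.** All references are to the protocol article.

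- *Cluster randomisation* gives a field rule: "45 households will be randomly selected in each cluster and five eligible household members recruited into the cross-sectional surveys". It introduces the rule with its basis: "With an average household size of six and the frequency of under 5 years being 14.3" per cent.
- *Sample size calculation* starts from "Thus, for 0.80 power the study requires a cluster size of 58", adds an allowance ("With an expected non-response and a loss to follow-up of 37" per cent), and concludes that "the sample size per cluster has been determined to be 80". It then multiplies up: "With 18 clusters to be surveyed, a total of 1440 study participants".
- Table 2, the trial registration data, repeats the total: "Target sample size 1440".
- *Sensitisation and recruitment* describes the household draw by random number generator: "households will be selected until the sample size for each village is attained". It gives no number of households.
- *Study outcomes and measurements* says that the primary outcome is measured by cross-sectional surveys at baseline and at 12, 24 and 30 months. These are the surveys to which the rule of 45 households and five members applies.

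**The concern.** The article gives two recruitment instructions for the same surveys, and a field team cannot follow both. One fixes the number of households and members. The other fixes the number of people per village and stops when it is reached.

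Three things depend on the answer:

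- **Workload and budget.** The sample size section says that power was set with the budget in mind, and the Discussion says that funds did not allow wider screening of communities.
- **Structure of the sample.** Eighty people can come from a few households taken almost whole, or from many households giving one or two people each. These samples differ in within-household clustering and in how widely the village is covered.
- **The registered target.** If the household rule is what was meant, 1440 is wrong wherever it appears.

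Baseline prevalence also defines the randomisation strata. If villages were sampled under different rules, the precision of the stratifying variable would differ between them.

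**Working it through.** **Inputs.** 45 households per cluster, five members, household size 6 and 14.3% under five years (*Cluster randomisation*); cluster size 58, allowance 37%, 80 per cluster, 18 clusters, total 1440, effect size 0.4, two-sided alpha 0.05 (*Sample size calculation*); target 1440 (Table 2).

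**1. Reproduce the plan's figure.** 58 x 1.37 = 79.46, rounded up to 80; 80 x 18 = 1440. Both match. The 80 therefore already contains the 37% allowance. Whether multiplying by 1.37 is the right inflation is a separate matter. Dividing instead, 58 / 0.63 = 92.06, gives 93, which is no closer to the household rule. The 58 cannot be re-derived because no ICC is stated.

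**2. Is five meant per household?** Age-eligible members per household: 6 x (1 - 0.143) = 5.14. Yes: the sentence derives five from household size. Five per cluster would give only 5 x 18 = 90 people in the trial.

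**3. Apply the household rule.** 45 x 5 = 225 per cluster; 225 x 18 = 4050. Ratio 225 / 80 = 2.81. Difference 4050 - 1440 = 2610 people per survey. If all four surveys were filled to that size, the difference would be 2610 x 4 = 10,440 person-surveys.

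**4. Can attrition reconcile them?** 225 x 0.63 = 142, which is neither 80 nor 58.

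**5. What would 80 per cluster need?**
- At five per household: 80 / 5 = 16 households per cluster, or 16 x 18 = 288 in all.
- At 45 households: 80 / 45 = 1.78 members per household.

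**6. Effect on power.** ICC assumed, because none is given. Two-level cluster-randomised formula with J = 18 clusters, n per cluster, effect size 0.4 and ICC rho: noncentrality = 0.4 x sqrt(J / (4 x (rho + (1 - rho)/n))), noncentral t with J - 2 = 16 degrees of freedom.

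| Assumed ICC | n = 58 | n = 80 | n = 225 |
|---|---|---|---|
| 0.03 | 0.957 | 0.972 | 0.990 |
| 0.05 | 0.871 | 0.893 | 0.928 |
| 0.08 | 0.730 | 0.750 | 0.784 |

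Going from 80 to 225 per cluster adds between 0.018 and 0.035 in these rows. The number of clusters limits power, so the extra people add little. The formula has no household level, and the article gives no within-household correlation, so the cost of five rather than 1.8 members per household is not quantified here.

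**The case against.** Several points can fairly be made on the other side.

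- **The two numbers may describe different samples.** The household rule names the cross-sectional surveys, *Secondary outcomes* has a longitudinal subsample of 80 individuals, and the figure of 58 returns in the analysis strategy for that subsample. So 225 might be cross-sectional and 80 longitudinal. This does not clear the conflict. The sample size section applies 80 to each of the 18 clusters and gives 1440 as the number expected in the trial, and Table 2 repeats it. On this reading 1440 would still be wrong. The objection does show that the intended correction cannot be presumed.
- **The recruitment section already settles it.** Selecting households until the village sample size is reached refers to the 80. This stands: it is not a third, competing rule but sits with the 80 and the 1440. It leaves the 45 x 5 instruction unexplained, since nothing calls the 45 households a ceiling or a reserve list.
- **Stopping early need not bias the sample.** At five per household, a team reaching 80 would leave 45 - 16 = 29 drawn households unvisited. If households are approached in the random order drawn, those visited are still a random set. This stands; the article states no visiting order, so bias is possible but not shown.
- **Power is hardly affected.** This stands. Both planned samples exceed 58 before attrition.

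A reader might also infer that 45 is simply a slip for 16, because five per household fits the household arithmetic. That arithmetic supports the five; it does not show that the 45 rather than the 80 is wrong.

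**Conclusion.** The contradiction is real and rests on figures that the article states. The household rule gives 225 per cluster and 4050 in total; the sample size section and the registered target give 80 and 1440, a factor of 2.8. Attrition, rounding and the longitudinal subsample do not reconcile them.

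The conclusion depends on one reading, that five members are taken from each household, which the sentence's own derivation supports.

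The consequence is for executability, workload, household clustering and the accuracy of the registered target. It would go too far to say that the trial is underpowered or the treatment comparison biased because of this. Over the assumed ICC range of 0.03 to 0.08, power is 0.97 to 0.75 with 80 per cluster and 0.99 to 0.78 with 225, and nothing in the article ties either rule to study arm. It still needs correction, because it governs recruitment into the surveys that measure the primary outcome.

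**What to change.** Make one figure govern.

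- **If 80 per cluster is intended**, change the *Cluster randomisation* sentence in one of two ways. Option one is about 16 randomly selected households with five eligible members each (16 x 5 = 80). Option two is 45 households with one or two eligible members chosen at random from each, averaging about 1.8 and capped at 80. Two from every household would give 45 x 2 = 90. Option two reduces household clustering for the same 80 people.
- **If 225 is intended**, correct the 80 and the 1440 in *Sample size calculation* and Table 2, and the registered target.

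In either case, align *Sensitisation and recruitment*: state that households are approached in the random order drawn until the target is met, or that all selected households are visited before recruitment closes. The second wording would replace the present stopping rule.

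**Cost.** The change is a few sentences and a matching field procedure. The 45-household option means 45 x 18 = 810 household visits rather than 288, or 522 more. The 225 option means 2610 more people per survey than the present target. Recruitment began on 19 May 2017, so the rule used so far in each village should be documented, and the correction filed with the ethics committees as an amendment if it is substantial, as the article itself provides.
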